### Statistical analyses

The statistical analysis will follow the intention-to-treat (ITT) principle. All eligible and consenting household members selected for outcome assessment will be analysed according to the randomised allocation of their village, regardless of intervention exposure, adherence, protocol deviations, or withdrawal from intervention activities. The village is the unit of randomisation, while outcomes are measured at the individual participant level. All analyses will therefore account for clustering at the village level. The allocation groups will remain masked to the statistician where feasible, until the primary analysis code and outputs are finalised. The primary comparison will be between villages allocated to the Saan Suk intervention and villages allocated to the current practice. All effect estimates will be presented with 95% confidence intervals. Statistical significance will be assessed using two-sided tests with an alpha level of 0.05.

A per-protocol analysis will be conducted as a sensitivity analysis. Here, we will include participants in intervention villages who received at least three or four planned visits, and participants in control villages with no documented exposure to Saan Suk-specific materials or training content.

Baseline characteristics will be summarised by cRCT arm to assess the comparability of the randomised groups and to describe the study population. Because randomisation is conducted at the village level, baseline balance will be assessed at both the cluster and individual levels. Cluster-level baseline characteristics include sub-district, distance to neighbouring study villages, number of registered VHVs, and relevant ecological characteristics, i.e., land use classes (e.g., vegetation, agricultural areas) and land-use interfaces where contact between people and wildlife may occur. Individual-level baseline characteristics will include age, sex, education, income, occupation category, household size, prior experience of zoonotic infectious diseases, and prior awareness of zoonotic diseases. The baseline assessment of the outcomes will not be conducted due to restricted operational feasibility. The background characteristics will be presented as means and standard deviations or medians and interquartile ranges for continuous variables, and as counts and percentages for categorical variables. Cluster size variation will be described and considered in sensitivity analyses.

The primary outcome is the total knowledge score at post-intervention assessment, treated as a continuous variable. Between-arm differences will be estimated using a linear mixed-effects model with identity link, consistent with the assumptions used for the sample size calculation. The model will include a fixed effect for trial arm (intervention vs control) and random intercepts for cluster (village) to account for within-cluster correlation. Pre-specified adjustment covariates include district, VHV ID, age group, sex, education category, and occupational category. Additional adjustment for further baseline variables will be considered if important imbalances are observed despite randomisation.

In addition to the total score, planned stratified analyses of domain-specific knowledge scores will be conducted using the same mixed-effects modelling framework. These analyses are considered exploratory and will not replace inference based on the total knowledge score. The intraclass correlation coefficient will be estimated for the primary outcome.

Secondary outcomes (behaviour, attitudes, self-efficacy, and contacts with zoonotic hosts) will be analysed using mixed-effects regression models appropriate to the scale and distribution of each outcome (e.g., linear mixed models for approximately continuous outcomes; ordinal or generalised linear mixed models for ordinal or non-normal outcomes). For all secondary analyses, cluster will be included as a random effect, and district and VHV will be included as fixed effects where relevant. Effect estimates will be reported with 95% CIs and two-sided p-values. All secondary analyses are exploratory and will be interpreted descriptively. No adjustment for multiple comparisons will be applied.

We do not anticipate substantial missing data due to the following established data collection and quality-control procedures: the data collection tool prompts for answers to each question before proceeding, all interviewers will be trained to complete all items, and data entries will be monitored daily by the field trial supervisor and data manager. If critical items are missing (especially for the primary outcome), participants will be re-contacted within a day. Nevertheless, the extent, patterns, and potential mechanisms of missing data will be systematically examined. If missingness is judged to be missing at random (MAR), missing data will be addressed using multiple imputation. The primary analysis will then be conducted on the imputed or weighted datasets as part of the sensitivity analyses. If missingness is not at random (MNAR), we will conduct sensitivity analyses using MNAR-suitable models, such as pattern-mixture models and delta-adjusted multiple imputation/tipping-point analyses.

Overall, the extent and pattern of missing data will be summarised by trial arm, village, and outcome. Reasons for missing data will be documented where available, including refusal, absence, withdrawal, incomplete questionnaire, loss to follow-up, or data collection error. We will compare participants with complete and incomplete outcome data using baseline socio-demographic characteristics, outcome values where available, village, intervention dose (number of received visits), and trial arm. To assess potential selection bias, we will describe and compare the household selection, consent, refusal, non-response, and loss-to-follow-up rates between trial arms and across clusters. Where information is available for non-participants or participants lost to follow-up, we will compare them with included participants to assess whether missingness or non-participation may be associated with allocation group or key baseline characteristics.

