Socio-demographic and experiential variables are collected to describe the study population and adjust for potential confounding. The questionnaire was reviewed by experts from Thailand and Europe and piloted with a small sample (n = 24) of the target population in November 2025, in Khon Kaen Province, Thailand, to assess its clarity and feasibility. Minor revisions were made before field implementation. The questionnaire was developed based on several key publications identified through a literature review, including PREDICT project questionnaires [36,37], WHO-UNICEF WASH household survey [38], and studies on health literacy among pet owners and livestock farmers, mosquito-borne diseases, wildlife trade, and bushmeat consumption in Africa [39] and Southeast Asia [40–43]. It is divided into five sections: (1) general information and participant ID generation; (2) knowledge, attitudes, self-efficacy, and behaviour related to zoonotic disease and spillover risk; (3) exposure to animal and environmental risks across different sites usually visit (home, temple, garbage dump, water body, agricultural field, and forest) and animal contacts reported; (4) socio-demographic and livelihood characteristics; and (5) contamination and process monitoring questions.

Primary and secondary outcomes will be assessed among recruited household members in both arms during the week following completion of intervention delivery. The Village Heads will invite participants to attend the assessment interview session in the community centre. The trained trial team will obtain informed consent when it has not been obtained previously. The interview will be conducted using a structured questionnaire and will last 45–60 minutes.

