**ASSESSMENT**												
Baseline variables* of household members				x								
Post-intervention outcome assessment in household members in the intervention arm										x	x	
Post-intervention outcome assessment in household members in the control arm										x	x	

*Variables are collected to compare arms and randomisation balance: age, gender, number of people in household, household income category, and number of ineligible people in household. The baseline does not include a full outcome assessment due to study feasibility constraints.

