We acknowledge that the implementation of the Saan Suk programme depends on the availability, motivation, and capacity of VHVs. VHVs are trusted community actors well placed to deliver household-level health education interventions; however, they may differ in experience, communication style, time availability, and confidence in delivering One Health content. To support intervention fidelity, VHVs in the intervention arm will receive standardised training during a two- to three-day workshop, including a manual, structured materials, and communication training. Adherence and fidelity will be monitored through visit documentation, conducted by VHVs and evaluated by the trial coordination team.

Village Heads will also play an important role in supporting trial implementation, including encouraging adherence to training and field procedures. Their involvement in the allocation process, including the public envelope draw, is intended to strengthen transparency, community acceptance, and local ownership. Village Head permission is necessary for the respective village participation in the study; however, individual informed consent will also be obtained from trial participants, including VHVs and adult household members, where they participate in study-specific procedures or outcome assessment.

Outcome assessment is based on self-reported information, including knowledge, attitudes, self-efficacy, behaviours, and contacts with local animal hosts. These outcomes are appropriate for evaluating behavioural determinants of zoonotic spillover prevention, but they are subject to self-report and social desirability bias, particularly after delivery of an educational intervention [44]. To reduce measurement bias, outcome assessors will be trained, standardised questionnaires will be used, and outcome assessment teams will remain blinded to the intervention allocation. The questionnaire was expert-reviewed, back-translated, and piloted in the target communities to improve clarity, cultural appropriateness, and acceptability. The questionnaire also includes items to collect information on potential baseline factors that may differ between the trial arms and, if necessary, can be adjusted for in the analysis. Non-self-reported outcomes of zoonotic disease prevention behaviour or spillover risk are not feasible within the scope of this trial.

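### Prior awareness and prior experience of zoonoses are listed as baseline variables but appear to be asked after the teaching, and nothing bars them from imbalance-triggered adjustment

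*Protocol article*

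**What the plan says.** The Statistical analyses section lists the individual-level baseline characteristics used to judge comparability of the arms. The list ends with "household size, prior experience of zoonotic infectious diseases, and prior awareness of zoonotic diseases". The same section states: "The baseline assessment of the outcomes will not be conducted due to restricted operational feasibility".

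The footnote to Table 2 names the variables collected in week 3 to compare arms: "age, gender, number of people in household, household income category, and number of ineligible people in household".

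The other participant instrument described is the structured questionnaire. On its timing, Primary and secondary outcomes says: "Primary and secondary outcomes will be assessed among recruited household members in both arms during the week following completion of intervention delivery". In describing this questionnaire, that section adds: "Socio-demographic and experiential variables are collected to describe the study population and adjust for potential confounding". According to the Discussion, this instrument holds "items to collect information on potential baseline factors that may differ between the trial arms and, if necessary, can be adjusted for".

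The pre-specified covariates for the primary model are district, VHV ID, age group, sex, education category and occupational category. The next sentence reads: "Additional adjustment for further baseline variables will be considered if important imbalances are observed despite randomisation".

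**The concern.** A baseline variable may be used to judge randomisation and to adjust the treatment comparison because treatment cannot have affected it. A question about prior awareness loses that property if it is put to people who have just been taught about zoonotic disease for four weeks. Some will report as prior what they have only now learned. Others may realise that they had not known before. Either way the arms can differ on the answer although randomisation worked.

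Two things are then at stake. The balance table could present a treatment effect as a chance baseline difference. And that difference could prompt an adjustment of the primary model, which would condition the estimate on a consequence of the intervention closely related to the outcome, knowledge of the same subject. With no baseline knowledge score, prior awareness is the listed variable nearest to one, and so a natural candidate.

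**Working it through.** **Timing.** Set side by side, the two baseline lists differ:

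- Statistical analyses: age, sex, education, income, occupation, household size, prior experience, prior awareness.
- Table 2 footnote (week 3): age, gender, household size, income, number of ineligible people.

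Education, occupation, prior experience and prior awareness are missing from the second list. The only other described source is the questionnaire, scheduled in Table 2 after the household visits. A four-week programme is unlikely to change education or occupation. It can change reported awareness. Experience is a past event, but teaching may alter its recognition and recall.

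**Route into the model.** Neither variable is in the pre-specified covariate list. Both are on the protocol's own list of baseline characteristics, so both fall within the further baseline variables that may be considered after an imbalance.

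**Size, illustration 1.** The planned effect reproduces: 0.40 × 15.23 = 6.09 points. Everything else here is an assumption, because the documents give no inputs, and clustering is ignored. Let k0 ~ N(0,1) be prior knowledge, balanced between arms, and T the arm (0 or 1). The score is 57.35 + 15.23(k0 + 0.4T). A person reports prior awareness if k0 + L × 0.4T + e > 0.3, with e of SD s. L is the share of the effect that leaks into the recalled answer; s sets how loosely the answer tracks knowledge.

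For a large sample:

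- adjusted effect = 6.09 − γ(p1 − p0), where p1 and p0 are the reported proportions in the intervention and control arms;
- γ = 15.23 × (mean within-arm covariance of k0 with the answer) / (mean within-arm p(1 − p));
- the within-arm covariance is φ(a)/v, with v = √(1 + s²) and a = (0.3 − 0.4LT)/v.

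Worked case, s = 1, L = 1:

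- v = 1.414, p0 = 0.416, p1 = 0.528.
- Covariances 0.2758 and 0.2814, mean 0.2786.
- Variances 0.2429 and 0.2492, mean 0.2461.
- γ = 15.23 × 0.2786/0.2461 = 17.24.
- Adjusted effect = 6.09 − 17.24 × 0.112 = 4.16, a change of −32%.

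The same formula gives:

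| Leakage L | s | Adjusted effect | Change |
|---|---|---|---|
| 0 | any | 6.09 | 0% |
| 0.25 | 1 | 5.61 | −8% |
| 0.5 | 1 | 5.13 | −16% |
| 1 | 2.5 | 5.56 | −9% |
| 1 | 1.5 | 4.90 | −20% |
| 1 | 1 | 4.16 | −32% |
| 1 | 0.75 | 3.62 | −41% |
| −0.5 (opposite recall) | 1 | 7.03 | +15% |

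For the last row, p1 = 0.362 and γ = 17.38, so 6.09 + 17.38 × 0.054 = 7.03.

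**Size, illustration 2.** A different model asks how far the result depends on the first. True prior awareness P is balanced. A share q of unaware intervention participants report awareness after teaching, and none do so in control. Aware people score g points higher. With P = 50%, q = 30% and g = 10:

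- p1 = 0.5 + 0.5 × 0.3 = 0.65, an apparent imbalance of 15 percentage points.
- γ = 10 × (0.25 + 0.175)/(0.25 + 0.2275) = 8.90.
- Adjusted effect = 6.09 − 8.90 × 0.15 = 4.76, a change of −22%.

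Over P of 30% or 50%, q of 10%, 30% or 50%, and g of 5, 10 or 15, the adjusted effect runs from 5.85 (−4%) to 2.31 (−62%).

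**The case against.** A reader might infer that the plan adjusts for these variables. It does not say that. Neither is pre-specified, and extra adjustment is only to be considered. The primary model as listed is free of the problem, and a statistical analysis plan, to which the Discussion refers but which is not shown, may settle which variables qualify. This stands, and it limits the point to a gap in the rule. It does not remove the point, because the protocol itself fixes the baseline list, the collection schedule and the trigger, and together they leave the route open. Masking the analysts does not close it, since an imbalance between masked groups is just as visible.

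A reader might also take the post-intervention timing as stated. It is inferred from the week-3 list and the absence of another described source. The item wording is not shown, and the questions may be anchored to a date before the programme. Such wording might reduce the influence of the teaching but could not be relied on to remove it.

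Finally, a reader might conclude that about a third of the effect would be lost. That figure assumes that the whole treatment effect leaks into a question about the past. With no leakage the bias is zero, and with the opposite recall pattern it is upward. Neither size nor direction is established, and no figure here applies to prior experience, which was not modelled.

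**Conclusion.** The point holds as a conditional risk to the primary estimate. Two variables called baseline appear to be measured after an intervention that can change the answers, and the imbalance rule does not exclude them. The case is clear for prior awareness and weaker for prior experience.

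The size is unknown. In the first illustration, with a true effect of 6.1 points, the change runs from 0% to about −41%. That is not a bound: the second model reaches −62% at its extreme, and opposite recall reverses the sign. All of this applies only if the adjustment is actually made. Without it, the consequence is a balance table that could be misread.

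**What to change.** - Limit any imbalance-triggered adjustment to variables measured before intervention delivery or that the intervention cannot plausibly change, such as education and occupation.
- State that prior awareness is not eligible, nor prior experience if it is asked after delivery.
- Show either in the balance table only if labelled as recalled after the intervention.

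This costs wording and one possible prognostic covariate. The pre-specified covariate list need not change on this account.

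Collecting both items beforehand in both arms is an alternative, with two conditions. Table 2 places week 3 after randomisation and starts the intervention-arm community meetings in that same week, so the items would have to be asked before those meetings. And under Informed consent, control participants consent individually only before the outcome assessment, so earlier questions are possible only if the consent arrangements allow them. The status section reports no enrolment at submission, so the wording change is best made before recruitment starts.

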## Materials and methods

### Aims, study design, and settings

We will implement the Saan Suk cRCT in rural villages of Chanthaburi province, eastern Thailand. We hypothesise that community members in villages allocated to the Saan Suk intervention will show better knowledge and understanding of zoonotic spillover, transmission pathways, risk factors, perceived susceptibility and severity, and preventive behaviours compared with community members in villages continuing the current practice. Therefore, the primary objective of the Saan Suk cRCT is to evaluate whether the Saan Suk educational programme (intervention) improves community members’ knowledge and understanding of zoonotic spillover, transmission pathways, risk factors, perceived susceptibility and severity, and preventive behaviours, as informed by the Health Belief Model, as well as socio-ecological drivers as informed by the One Health approach. The secondary objectives of the Saan Suk cRCT are to: 1) assess changes in attitudes, perceived susceptibility, and perceived severity of zoonotic disease risks, in line with the Health Belief Model; 2) assess whether the intervention changes self-reported preventive behaviours that reduce direct and indirect contact with wildlife, domestic animals, and potentially infectious animal tissues; and 3) evaluate whether hands-on training and skill-building delivered by VHVs enhances community members’ self-efficacy to translate knowledge into preventive practices.

The Saan Suk trial is a parallel-arm, cluster-randomised superiority trial evaluating the effectiveness of the Saan Suk intervention on the primary and secondary outcomes. Villages are the unit of randomisation and the Saan Suk intervention allocation. Villages will be allocated equally, i.e., using an 1:1 ratio, to the intervention or control arm using simple randomisation. The cluster design was selected to minimise intervention spillover between participants living in the same village and to reflect the planned mode of intervention delivery through village-level health structures.

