### Sample size calculation

The sample size for the Saan Suk cRCT was calculated based on the primary outcome, i.e., the knowledge score, scaled to 0–100. Parameters were derived from a cross-sectional survey conducted in Chanthaburi in November 2024 (n = 687), with a resulting mean knowledge score of 57.35 and standard deviation (SD) of 15.23. An intracluster correlation coefficient (ICC) of 0.028 was obtained by fitting a random-intercept linear mixed-effects model with village as the clustering variable. Assuming a two-sided significance level of α = 0.05 and 90% power, the trial is powered to detect differences in mean knowledge scores between the intervention and control arms at the post-intervention assessment. We parameterised the expected effect using Cohen's *d* of 0.40 [35], corresponding to approximately six points on the 0–100 knowledge scale, based on the estimated SD from the cross-sectional survey. This effect size is considered a small-to-moderate improvement in educational intervention research, and it is viewed as a meaningful and achievable change in population knowledge over a short period.

Sample size adjustments accounted for clustering, a 15% allowance for both individual- and cluster-level attrition, and a 5% inflation to account for potential contamination. Based on these assumptions and operational feasibility, the final design includes 24 clusters (villages), with 12 clusters per arm, with an average cluster size of 42 participants (i.e., 6 VHVs per village, visiting 7 households each), resulting in a total sample size of 1008 individuals (504 per arm) (Fig 1).

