### Participants

Villages (clusters) and VHVs delivering the intervention will be assessed for eligibility based on the following inclusion and exclusion criteria. Villages will be eligible if (1) they are classified as rural and located within the study area; (2) they have at least six active VHVs; (3) they are accessible by vehicle (a van); (4) they are located at least 2 km from other participating villages; (5) their Village Heads provide written informed consent; and (6) they are considered feasible for study implementation based on prior scoping visits and survey data. Villages will be excluded if they meet any of the following criteria: (1) located in urban areas or outside the study area; (2) not feasible for implementation due to security concerns (e.g., armed conflict, civil unrest) or lack of governmental approval; or (3) located less than 2 km from another participating village.

VHVs will deliver the Saan Suk educational programme to participating households in their assigned villages. VHVs will be eligible if they meet all of the following criteria: (1) are currently active in their role and regularly serving at least seven households; (2) have been living in the selected village for at least six months prior to enrollment and intending to remain for the duration of the trial; (3) are registered in the national VHV registry; (4) participate in routine VHV training at the local hospital; (5) are aged ≥18 years; (6) are able to provide informed consent; and (7) are willing to participate in a 2–3 days training programme. VHVs will be excluded if they meet any of the following criteria: (1) are unable to provide informed consent; or (2) decline or withdraw consent at any stage of the study.

Households are eligible if they are permanent households in a participating village, are assigned to a VHV included in the trial procedures, have at least one adult household member aged 18–80 years, and the Household Head provides informed consent for household participation. Households are not eligible if they are uninhabited or not permanently occupied, are assigned to a VHV not included in the trial procedures, have no household member aged 18–80 years, or the Household Head does not provide consent.

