As this trial involves a non-clinical educational intervention, no medical risks are anticipated. However, criteria are defined for discontinuing or modifying the allocated intervention at the individual, provider, and trial levels. For households and individuals, we will discontinue (stop all remaining study visits for that household) if any of the following occur: (1) participant or household head requests to stop participation at any time, for any reason (no justification required); (2) any safety event during or within 24 hours after a visit that poses immediate risk to the participant, household member, or VHV (e.g., physical aggression, threats, severe dog bite or animal attack, hazardous environment); (3) serious adverse event plausibly related to the visit (e.g., injury while acting on a demonstration); (4) confidentiality concern that cannot be mitigated; and (5) loss of eligibility, such as when a participant moves away or lacks capacity to consent. Discontinuation may also occur following a request from VHVs, community leaders, or local authorities. At the VHV level, the intervention delivery will be discontinued if any of the following occur: (1) the VHV fails competency checks after training, (2) breaches confidentiality, or (3) is implicated in a safety-related complaint. In such cases, households will be reassigned to another trained VHV within the same village where feasible. If reassignment is not possible, the intervention will be modified (e.g., delivered in leaflet-only format by a supervisor) or discontinued, and this will be documented as a delivery limitation rather than a crossover.

At the trial level, cRCT may be discontinued (1) in case of major logistical, environmental, political, and civil unrest barriers preventing continuation of the study procedures, (2) ethical or safety concerns raised by the Ethics Committee or relevant authorities, or (3) external events such as natural disasters or public health emergencies that make study implementation unsafe. Discontinuation may also occur if there is (4) an inability to enrol or retain clusters or participants at a sufficient rate to ensure trial completion, (5) loss of implementing partners or VHV network capacity, or (6) data quality failure compromising interpretability, such as when more than 20–30% of primary outcome data are missing.

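### The primary model lists VHV ID as an adjustment covariate, but each VHV belongs to one village and so to one arm; entered as a fixed effect, it makes the arm effect inestimable

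*Protocol article*

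**What the plan says.** The primary analysis (Statistical analyses) is a linear mixed model for the total knowledge score, with a fixed effect for arm. The only random term it names is an intercept for village. It then adds: "Pre-specified adjustment covariates include district, VHV ID, age group, sex, education category, and occupational category". The domain-score analyses use the same framework.

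For the secondary outcomes the same section says that "cluster will be included as a random effect, and district and VHV will be included as fixed effects where relevant".

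Other sections fix how VHVs relate to villages and arms:

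- Aims, study design, and settings: "Villages are the unit of randomisation and the Saan Suk intervention allocation".
- Participants: an eligible VHV must "have been living in the selected village for at least six months prior to enrollment", and "VHVs will deliver the Saan Suk educational programme to participating households in their assigned villages".
- Sample size calculation: "6 VHVs per village, visiting 7 households each", in 24 villages, 12 per arm.
- Intervention and comparator, if a VHV has to be replaced: "households will be reassigned to another trained VHV within the same village where feasible".
- Data management plan: each VHV receives a unique identification code.

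**The concern.** Together these statements make VHV strictly nested in village, and village nested in both arm and district. No VHV serves households in both arms. A fixed effect for each VHV therefore uses up every between-village difference, and the difference between arms is one of them. Nothing is left from which to estimate the arm effect.

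This model carries the trial's only confirmatory test. Followed literally, it gives either no treatment estimate or one that depends on the order in which the software meets the columns. The team would then have to depart from its published primary model, and choose a replacement, in the one analysis where pre-specification matters most.

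**Working it through.** **Inputs.** From Sample size calculation: 24 villages, 12 per arm; 6 VHVs per village; 7 households per VHV; SD 15.23; ICC 0.028; d = 0.40, about 6 points. I take one respondent per household, which reproduces the plan's total: 24 × 6 × 7 = 1,008, or 504 per arm.

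**1. Rank of the fixed-effect matrix.** Let V_k be the indicator for VHV k, k = 1 to 144. Then

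- arm = sum of V_k over the 72 VHVs in intervention villages;
- district = sum of V_k over the VHVs in one of the two districts.

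Both are exact linear combinations, whichever villages are drawn to which arm.

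| Fixed-effect columns | Number | Rank |
|---|---|---|
| Intercept + 143 VHV indicators | 144 | 144 |
| The same + arm + district | 146 | 144 |

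Adding age group, sex, education and occupation (4, 2, 4 and 4 categories assumed) does not help. Without arm there are 155 columns of rank 154; with arm there are 156, still of rank 154. The residual sum of squares of arm is zero to machine precision once the VHV indicators are in, against about 250 without them.

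**2. The village random intercept.** It does not rescue the model. The VHV indicators also span all differences between villages, so the village variance, and an ICC taken from this model, are not identifiable.

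**3. What software would return.** If arm is entered after VHV, arm is dropped or the fit stops. If arm is entered first and redundant columns are dropped in order, two VHV indicators go. The arm coefficient is then the mean of one VHV's 7 respondents minus the mean of another VHV's 7.

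- Reported SE: 15.23 × √(1 − 0.028) × √(2/7) = 8.03 points.
- Actual sampling SD, because the two VHVs sit in different villages: 15.23 × √(2 × (1 + 6 × 0.028)/7) = 8.80 points.
- Rejection at a true 6 points: the critical value is about 1.96 × 8.03 = 15.7. P(estimate > 15.7) + P(estimate < −15.7), for a normal estimate with mean 6 and SD 8.80, is about 0.13 + 0.01 = 0.14. A simulation of 1,000 trials gave 14.4%, with a mean reported SE of 8.01.

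**4. The intended comparison.** Without VHV ID the matrix has full rank (13 of 13 columns under the same assumed categories).

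- Design effect: 1 + 41 × 0.028 = 2.148.
- SE: 15.23 × √(2 × 2.148/504) = 1.41 points. Simulation of village means gave 1.44, with a mean estimate of 6.05 for a true 6.
- Power at 6 points: 6/1.41 ≈ 4.3 standard errors, which is about 98% on a t distribution with 22 degrees of freedom.

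**The case against.** The strongest reply is that the primary-model sentence does not call VHV ID fixed. It calls it an adjustment covariate, and a random VHV intercept nested in village would leave the arm effect estimable. That is true, but the text does not say so. It lists VHV ID beside sex and district, names village as the only random term, and calls VHV a fixed effect in the secondary models. If a random term was meant, the wording still has to change. Coding VHVs 1 to 6 within each village would also restore rank, but volunteer 3 in one village has nothing in common with volunteer 3 in another, and the protocol assigns unique codes.

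Four narrower points stand:

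- The secondary rule is qualified to apply where relevant, and those analyses are declared exploratory, so the damage there is smaller.
- The protocol does not tie its promised ICC to the VHV-adjusted model. A model without VHV terms would still supply it.
- The aliasing follows from the layout alone. It can be seen on a dummy dataset before any outcome exists, and many packages would warn of it. The departure from plan need not be driven by data.
- The 8.0-point SE and 14% rejection describe one software behaviour. The rank result is the evidence; these figures illustrate it.

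An unseen analysis plan may specify the term differently. That would not cure the protocol, which already states a specific covariate list as pre-specified.

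**Conclusion.** The concern holds, and the wording must be fixed before the analysis. With VHV ID as a fixed factor, the primary model cannot estimate the treatment effect. This is an algebraic result that needs no assumed SD, ICC or effect size. It rests on three things: VHV ID is fixed, VHVs are uniquely coded, and each VHV serves one village. The protocol supports the last two directly and the first by its natural reading.

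The practical size depends on software. At worst an arm coefficient is reported with nearly six times the intended standard error (8.03/1.41 ≈ 5.7), and it compares two volunteers, not two arms. The domain-score analyses inherit the problem, as does any secondary model in which VHV is entered as fixed. District is redundant in the same way once VHV indicators are present.

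**What to change.** Change two sentences in Statistical analyses.

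- **Primary model:** remove VHV ID from the adjustment covariates. Keep arm, district, age group, sex, education and occupation as fixed effects, with a random intercept for village.
- **Secondary models:** remove VHV from the fixed effects, so that the sentence matches the primary model.
- **If clustering by volunteer is of interest:** state a second random intercept, for VHV nested in village, in both places. It adds no fixed-effect columns, so arm stays estimable.

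The statistical analysis plan should be checked for the same wording, and the code run on a dummy dataset with the planned layout before database lock.

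The cost is a short amendment. Sample size, fieldwork and data collection are unaffected, VHV ID is still recorded, and the protocol reports that nobody had been enrolled at submission.
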